### Blind assessments

The blind assessor will contact the patient via phone call every six weeks during the six months of the study, for a total of four times (see Table 2). The instruments administered during each blind assessment will include the HAM-D-17, CGI-S, CGI-I, and Q-LES-Q. In addition, patients receiving mental healthcare from their PCPs will also be asked about their treatment response and adherence and medication side effects. Although this information will also be collected by patients' care managers for those in the intervention group, the information gathered by the blind raters will be used for data analysis (the information gathered by care managers is used more for clinical purposes).

**Table 2 T2:** Timeline for Blind Assessment

Blind	6 wk	12 wk	18 wk	24 wk or endpoint	
Interviewer					
HAM-D-17	X	X	X	X	
CGI-S, CGI-I (subject and interviewer rated)	X	X	X	X	
Q-LES-Q	X	X	X	X	
Adherence, PCP Treatment*	X	X	X	X	
Adherence, Medication*	X	X	X	X	
Adverse Events*	X	X	X	X	

*Only for patients receiving antidepressant treatment from their PCPs

### Analysis

For all hypotheses tested, an "intent to treat" analysis examining all patients randomized to the trial will be performed to preserve the effect of randomization. Random effects linear regressions (for continuous outcomes measured repeatedly) and random effects logistic regressions (for binary outcomes measured repeatedly) will be performed to detect associations between interventions and outcomes, controlling for relevant covariates. Random effects models for repeated measures will be used, since multiple assessments will take place throughout the study. Binary outcomes that are not measured repeatedly, like treatment initiation or trial completion, will be analyzed using multivariate logistic regressions. Relevant covariates that will be controlled for in all random and fixed effect regressions include the HAM-D-17 score at the baseline visit, the use of alternative treatments for depression, study site, and gender.

One of the major goals of the study is to test the null hypothesis that the proportion of responders in the T-CSCT group is equal to the proportion of responders in the usual care group. Assuming a sample size of 48 (60 enrolled per group, with 20% attrition), an alpha of 0.05, and a two-sided alternative hypothesis, the study will have power of 0.80 to detect a statistically significant difference between the proportions of responders in the two treatment arms. This computation assumes that the difference in proportions of treatment response is 0.30 (at least 70% of patients receiving T-CSCT will meet criteria for treatment response and up to 40% of patients in the control group will meet criteria for treatment response).

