## Methods/Design

Chinese Americans who screen positive for depression in participating primary care clinics will be called by research assistants. Eligible and interested patients will then be randomized into one of two groups. Those in the T-CSCT group will receive telepsychiatry-based Culturally Sensitive Collaborative Treatment (T-CSCT) from a multidisciplinary team, while patients in the Usual Care (UC) group will continue to receive treatment as usual from their PCPs alone. The proposed sample size is 60 patients in each group. However, anticipating a dropout rate of 20%, we aim to have at least 48 patients in each group complete all study procedures through the final week of the study.

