### Screening/Baseline Visit

In addition to the CB-PHQ-9, other instruments administered at the screening/baseline visit will include the Hamilton Rating Scale for Depression (HAM-D 17-item), the Clinical Global Impressions-Severity (CGI-S) and Improvement (CGI-I), the Quality of Life Enjoyment and Satisfaction Questionnaire (Q-LES-Q), the 16-item, Quick Inventory of Depressive Symptomatology (QIDS-SR) and the Explanatory Model of Interview Catalogue. The MINI, and the EIP (for patients in the T-CSCT arm) [22] will be administered by the clinician via videoconferencing at the screening visit.

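### HAM-D-17 is the only baseline score named for every model, so the Q-LES-Q and CGI-S analyses may forgo precision from their own screening values

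*Protocol article*

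**What the plan says.** The Analysis section plans random effects linear regressions for continuous repeated outcomes and random effects logistic regressions for binary ones. It then states that the covariates controlled for "in all random and fixed effect regressions include the HAM-D-17 score at the baseline visit", followed by use of alternative treatments, study site and gender. HAM-D-17 is the only baseline score in that list.

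The Screening/Baseline Visit section also collects "the Clinical Global Impressions-Severity (CGI-S) and Improvement (CGI-I), the Quality of Life Enjoyment and Satisfaction Questionnaire (Q-LES-Q"), and Table 1 marks the same instruments at the screening column, with CGI-S and CGI-I sharing one row. For follow-up, the Blind assessments section says: "The instruments administered during each blind assessment will include the HAM-D-17, CGI-S, CGI-I, and Q-LES-Q". Table 2 places these at weeks 6, 12, 18 and 24.

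The article does not say that each outcome is adjusted for its own baseline, and it does not rule this out. It also does not say whether the screening value enters the repeated-measures models as a first time point, or what a screening CGI-I is rated against.

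**The concern.** A scale's own starting value is usually a better predictor of its later values than the starting value of a different scale. Taken as written, the covariate list gives a Q-LES-Q model that adjusts for depression severity and not for the patient's starting quality of life, and a CGI-S model that adjusts for HAM-D-17 and not for starting CGI-S. Both own-baseline values are already collected.

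What is at stake is efficiency on these outcomes. Chance imbalance between arms on the scale itself would be only partly removed, and the confidence interval could be wider than it need be. With 48 completers planned per arm there is little precision to spare.

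The screening CGI-I is a separate and smaller matter. It is an improvement rating scheduled at the first visit, and no earlier state is given for comparison. It costs no precision, but it would have no clear meaning if it were carried into a model as a baseline or first time point.

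**Working it through.** **The plan's own figure.** The inputs, from the Analysis section, are "Assuming a sample size of 48 (60 enrolled per group, with 20% attrition), an alpha of 0.05, and a two-sided alternative hypothesis". The assumed response rates are 0.70 under T-CSCT ("at least 70% of patients receiving T-CSCT will meet criteria for treatment response") against 0.40 under usual care ("up to 40% of patients in the control group will meet criteria for treatment response"). The claim is that "the study will have power of 0.80 to detect a statistically significant difference between the proportions of responders".

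- Dropout: 48 / (1 − 0.20) = 60 per arm, which matches Methods/Design ("The proposed sample size is 60 patients in each group").
- Fisher's exact test, enumerated over all outcomes with 48 per arm: power 0.800.
- Normal approximation with continuity correction: pooled proportion 0.55; SE under the null = √(2 × 0.55 × 0.45 / 48) = 0.1016; SE under the alternative = √((0.21 + 0.24) / 48) = 0.0968; power = Φ((0.30 − 1/48 − 1.96 × 0.1016) / 0.0968) = 0.796.
- Without the correction, the pooled normal approximation gives 0.851.

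The stated 0.80 is therefore reproduced. It uses no covariates, so nothing below changes it.

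**Effect of adding the own baseline.** The documents give no correlations and no effect size for Q-LES-Q or CGI-S. The following are assumptions, for one post-baseline time point, with outcome variance set to 1:

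- r_c = 0.3: baseline HAM-D-17 with the follow-up outcome
- r_b = 0.5: baseline HAM-D-17 with the outcome's own baseline
- r_o = 0.3, 0.5 or 0.7: own baseline with the follow-up outcome
- a treatment effect of 0.5 SD, with 48 per arm

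Residual variance with HAM-D-17 only: V1 = 1 − r_c² = 1 − 0.09 = 0.91.

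Residual variance with both baselines: V2 = 1 − (r_o² + r_c² − 2 r_o r_c r_b) / (1 − r_b²).

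Power = Φ(0.5 / √(2V / 48) − 1.96).

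| r_o | V2 | V2 / V1 | SE ratio | Power, HAM-D-17 only | Power, both |
|---|---|---|---|---|---|
| 0.3 | 1 − 0.09/0.75 = 0.880 | 0.97 | 0.98 | 0.73 | 0.74 |
| 0.5 | 1 − 0.19/0.75 = 0.747 | 0.82 | 0.91 | 0.73 | 0.81 |
| 0.7 | 1 − 0.37/0.75 = 0.507 | 0.56 | 0.75 | 0.73 | 0.93 |

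In the middle row the gain equals having 48 / 0.82, or about 58, patients per arm in place of 48.

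**A case with no gain.** Let HAM-D-17 predict the outcome better than its own baseline does: r_c = 0.4, r_o = 0.3, r_b = 0.7. Then V1 = 1 − 0.16 = 0.840 and V2 = 1 − (0.09 + 0.16 − 0.168) / 0.51 = 0.839, a ratio of 0.999.

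Across these assumed values the variance reduction runs from about 0% to 44%.

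**The case against.** The strongest reply is that the list is open. It is introduced by the word include and reads naturally as the covariates common to all models, so own-baseline adjustment is not excluded. Screening might also enter the repeated-measures models as the first time point, in which case each scale's own baseline would already be used. This is a condensed article, and outcome-by-outcome model specification is commonly left to a fuller document. This much stands: a reader might infer that precision will certainly be lost, and the text does not support that. What remains is that the article does name a baseline score for all regressions, and names only one. Because baseline HAM-D-17 is a covariate in every model, including the HAM-D-17 model, baselines appear to be meant as covariates and not as time points, though this is not stated.

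The second reply is that little depends on it. Baseline HAM-D-17 is a valid covariate in a randomised comparison, so there is no bias. The HAM-D-17 models already carry their own baseline, the responder comparison is powered without covariates, and the Analysis section states no specific hypothesis for Q-LES-Q or CGI-S. All of this stands.

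The third reply is that the size is assumed throughout. This also stands: the calculation takes a single time point where the plan has repeated measures, and the gain can be nil.

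On CGI-I, a reader might infer that the screening value will distort the analysis. No section says that it is analysed or used as a baseline, so this cannot be claimed.

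**Conclusion.** The point holds as a modest, conditional one about efficiency. If the covariate list is applied as written, the Q-LES-Q and CGI-S models leave out a baseline value that is already in hand. The cost in variance depends on correlations the documents do not give: adding the own baseline multiplies the treatment-effect variance by 0.97, 0.82 or 0.56 under the three assumed own-baseline correlations, and by about 1.0 under less favourable values. No stated figure is wrong, no estimate is biased, and the HAM-D-17 and responder analyses are untouched.

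The CGI-I entry at screening is a separate minor scheduling flaw with no effect on precision. It is worth correcting because the article gives the rating nothing to refer to.

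**What to change.** In the Analysis section, add a sentence stating that each continuous repeated outcome is adjusted for its own screening value (Q-LES-Q for Q-LES-Q, CGI-S for CGI-S), with baseline HAM-D-17 kept as a covariate in all models, and that screening CGI-S is the baseline covariate for CGI-I. If screening values are meant to enter as the first repeated measurement instead, the section should say so.

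Separately, state that CGI-I is analysed only at weeks 6 to 24 and remove it from the list in the Screening/Baseline Visit section. In Table 1, relabel the shared row as CGI-S only. Deleting the screening mark would also remove the CGI-S value that the adjustment needs.

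The cost is a sentence, a text edit and a row label. No new data or patients are needed, and each model gains at most one parameter. The wording should be settled before outcome data are seen.

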### 5) Telephone-based care management to patients with depression

Care management has been found to be very effective in improving treatment adherence and general outcomes of depression; patients also tend to report higher satisfaction with their depression treatment when they are receiving collaborative care management [15]. Collaborative care management is ideal for patients whose grasp of the American healthcare system and the English language may make it difficult for them to navigate a complex treatment regimen.

Researchers found that implementing the CSCT model in a primary care setting greatly increased the number of Chinese American patients who were diagnosed with depression and subsequently engaged in treatment, with 6.5% of depressed Chinese Americans receiving psychiatric treatment before and 43% after. In addition, patients in both care management and treatment as usual groups demonstrated a good response to treatment, although no significant differences were found between the treatment outcomes of the patients in the two groups [2]. Further research is needed to clarify why patients receiving care management did not experience even better outcomes than patients in the usual care group. One possible explanation is that PCPs in this study frequently referred study patients in both groups back to psychiatrists for treatment, so patients in both groups were receiving active psychiatric treatment that was not a part of the intervention being tested in the study.

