### Description of T-CSCT Intervention

The T-CSCT intervention involves two major components:

1)T-CSCT assessment: Patients in the T-CSCT group will undergo a telepsychiatry-based culturally sensitive psychiatry assessment by a bilingual psychiatrist using the Engagement Interview Protocol (EIP), described above. Patients in the UC arm will also undergo the initial telepsychiatry-based assessment with a psychiatrist, but this assessment will not utilize the EIP.

2) Care management: The goal of care management is to monitor patients' psychiatric treatment as well as to consolidate and streamline the treatment efforts of the patient's PCP and psychiatrist. Via regularly scheduled phone visits with patients, bilingual care managers will monitor the following: patients' depressive symptoms, adherence to the MDD treatment protocol that their doctor(s) recommended, adverse events (for patients taking antidepressant medications), and patients' self-management of their depression. Care managers are accessible to patients through telephone contact or videoconferencing for questions on depression and medication, and they also can provide culturally sensitive interpretations of patients' symptoms and their treatment for depression. They serve as a link between the patient, PCP, and the consulting psychiatrist.

The first care management interview is a face-to-face meeting with a bilingual care manager to establish rapport and to explain the roles of care manager and blind assessor (see below for details on the blind assessments), as well as to review the patient's course of illness and provide an explanation of MDD and how it can be treated.

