Subsequent visits will take place via telephone at seven scheduled points throughout the study (see Table 1), but care managers will make additional phone calls if deemed clinically necessary and/or helpful to patients. During each phone visit, patients' depressive symptoms will be monitored using the CB-PHQ-9. When modification in treatment is needed, the care manager will send a report to patients' PCPs with recommendations from the study psychiatrist, who will provide weekly supervision to care managers. The study psychiatrist will be available for consultation via videoconference if requested by patients, care managers, or patients' PCPs. Care managers will encourage PCPs to consider the reports on the updates of patients' conditions when deciding whether to modify patients' treatment, and they will support PCPs in implementing these recommendations. Patients who do not respond to treatment by week 10 and those who have more complicated psychiatric illnesses (e.g., psychiatric comorbidities, past treatment failures) will be encouraged to have an additional psychiatric consultation via videoconferencing.

**Table 1 T1:** Timeline for Administration of Instruments by the Care Manager

Care Manager	Screen	^#^2 wk	^#^4 wk	^#^8 wk	^#^12 wk	^#^16 wk	^#^20 wk	^#^24 wk
CB-PHQ-9	X	X	X	X	X	X	X	X
HAM-D-17	X							
CGI-S, CGI-I	X							
Q-LES-Q	X							
Adherence, PCP Treatment*	X	X	X	X	X	X	X	X
Adherence, Medication	X	X	X	X	X	X	X	X
Adverse Events*	X	X	X	X	X	X	X	X

^# ^Care Manager will provide 8 scheduled visits to subjects in the T-CSCT Group

*Only for patients receiving antidepressant treatment from their PCPs

For patients who are receiving concurrent treatment from their PCPs, care managers will assist in scheduling follow-up visits at approximately weeks 1, 3, 6, 10, 16, and 22 of the study in order for PCPs to monitor patients' treatment response, titrate medication dosages, and manage side effects of the medications.

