### Definition of Usual Care (UC)

PCPs of the patients who are randomized to UC will be informed that their patient is participating in the study and that the patient has depression. Patients will *not *receive protocol-driven collaborative care management; however, they may seek psychotherapy and/or psychopharmacological consultation, including a telepsychiatry-based consultation from the study psychiatrist.

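### Every regression adjusts for use of alternative treatments without limiting it to use before randomisation, so the intent-to-treat estimate can be biased

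*Protocol article*

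**What the plan says.** The Analysis section of the protocol article sets an intent-to-treat analysis "examining all patients randomized to the trial will be performed to preserve the effect of randomization". It then fixes the adjustment set for every random and fixed effect regression: "the HAM-D-17 score at the baseline visit, the use of alternative treatments for depression, study site, and gender". The same section names further outcomes that these models cover: "Binary outcomes that are not measured repeatedly, like treatment initiation or trial completion, will be analyzed using multivariate logistic regressions".

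Four other places bear on when other treatment can occur and in whom:

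- *Definition of Usual Care (UC)*: control patients get no care management, but "they may seek psychotherapy and/or psychopharmacological consultation, including a telepsychiatry-based consultation from the study psychiatrist".
- *Description of T-CSCT Intervention*: care managers follow, among other things, "adherence to the MDD treatment protocol that their doctor(s) recommended".
- The same description: patients without a response by week 10, and those with more complicated illness, "will be encouraged to have an additional psychiatric consultation via videoconferencing".
- *5) Telephone-based care management to patients with depression*: a possible reason for the earlier trial's null comparison is that PCPs often referred patients back to psychiatrists, "so patients in both groups were receiving active psychiatric treatment that was not a part of the intervention being tested in the study".

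The article does not define alternative treatments. It names no instrument for them in *Screening/Baseline Visit*, Table 1 or Table 2.

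**The concern.** Adjusting a randomised comparison for a variable measured before allocation is harmless and often helpful. Adjusting for one that allocation can change is different in kind. If the variable carries part of the effect, the arm coefficient loses that part. If patients with a poor outlook are more likely to seek other care, holding use constant compares patients of unequal prognosis across the arms, and randomisation no longer protects the contrast.

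Three of the four listed covariates cannot be changed by allocation. Use of alternative treatments can be, if it is counted during follow-up, and nothing in the text rules that out. At stake is the estimate from every adjusted effectiveness model. The trial is also partly about engagement in treatment (the Background names it in the primary goal), so the adjustment may remove some of what the intervention is meant to change.

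**Working it through.** **1. The plan's own figure.** The article states power 0.80 for 48 evaluable patients per arm, 70% against 40% response, two-sided alpha 0.05. Fisher's exact test gives 0.800 and the continuity-corrected normal formula 0.796 (uncorrected 0.851). The enrolment figure also reproduces: 48 / (1 - 0.20) = 60 per arm. The choice of covariates does not alter these figures. They matter here only because 30 percentage points is the planned effect.

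**2. Timing of the four covariates.**

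| Covariate | Time point in the text | Can allocation change it? |
|---|---|---|
| HAM-D-17 | baseline visit | no |
| Study site | none needed | no |
| Gender | none needed | no |
| Use of alternative treatments | none given | yes, if counted after randomisation |

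**3. Whether follow-up use can depend on arm and prognosis.** Usual-care patients without a care manager may look elsewhere. T-CSCT patients have a care manager and, if they have not responded by week 10, are encouraged towards a further consultation. That second route depends on response after randomisation. *Inclusion/Exclusion Criteria* excludes patients treated by a psychiatrist in the past four months, so recent psychiatric care would vary mainly after entry.

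**4. The algebra.** For a linear model with arm and use only, least squares gives exactly

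unadjusted effect = adjusted effect + g × (p1 - p0),

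where p1 and p0 are the proportions using other treatment in the T-CSCT and usual-care arms, and g is the coefficient of use in the adjusted model. Adjustment leaves the effect alone if p1 = p0 or g = 0. Otherwise it shifts the effect by -g × (p1 - p0). The sign of g is open: positive if use helps, negative if users have a worse outlook.

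**5. Illustration. All inputs are assumptions; none comes from the article.** One million patients per scenario; outcome is improvement in residual SD units; U is standard normal poor prognosis not captured by other covariates.

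- logit P(use) = -0.4 + aT × arm + aU × U
- outcome = bT × arm + bA × use + bU × U + error, error SD 1
- In (a) to (d) and (f), aU = 0.8 and bU = -0.7. In (e), both are 0.
- aT = 0 in (a), -1 in (b) to (e), +1 in (f). bT = 0 in (c), otherwise 0.5. bA = 0 in (b) and (c), otherwise 0.3.

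| Scenario | Use, UC / T-CSCT | Unadjusted (total effect) | Adjusted for use |
|---|---|---|---|
| (a) use unaffected by arm, as if fixed before randomisation | 41% / 41% | 0.498 | 0.498 |
| (b) UC seeks more; use tracks poor prognosis, no effect of its own | 41% / 22% | 0.500 | 0.406 |
| (c) as (b), no treatment effect | 41% / 22% | -0.002 | -0.096 |
| (d) as (b), use helps by 0.3 | 41% / 22% | 0.443 | 0.406 |
| (e) UC seeks more; use helps, unrelated to prognosis | 40% / 20% | 0.435 | 0.496 |
| (f) T-CSCT raises use; use helps and tracks poor prognosis | 41% / 63% | 0.562 | 0.602 |

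Checks by hand. In (e) the total effect should be 0.5 + 0.3 × (0.20 - 0.40) = 0.44, and the adjusted model should return the direct effect 0.5; both do within simulation error. In (b) the identity gives g = (0.500 - 0.406) / (0.22 - 0.41) = -0.49: users do worse only because they were sicker.

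**6. Response scale (again assumed inputs).** A latent normal outcome was cut to give 40% response in controls, and linear probability models were fitted. With use 60% in T-CSCT and 25% in UC, helping by 0.7 SD, plus a direct effect of 0.4 SD, a total difference of 24 points is reported as 15. With use 20% and 40%, helping by 0.5 SD, plus a direct effect of 0.6 SD, 19 points becomes 23. With no effect, use 20% and 40%, and sicker patients seeking more, 0 becomes about -4, or -6 to -7.5 under stronger confounding.

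The first of these shrinks the effect while (f) inflates it, though T-CSCT raises helpful use in both. The difference is the sign of g: in (f), g = (0.562 - 0.602) / (0.63 - 0.41) = -0.18, because users there are sicker.

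**7. Treatment initiation.** Here the outcome is uptake of treatment. Adjusting it for use of other treatment conditions one form of help-seeking on another, possibly over the same period.

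**The case against.** The strongest reply is that the text is ambiguous, not wrong. The other three covariates are fixed before allocation, so a baseline reading of the fourth is natural. The document is a condensed article, and the timing of a covariate is commonly left to the analysis plan. Under that reading, row (a) applies and there is no bias. This stands so far as it goes: the bias is conditional.

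Four stronger readings are tempting, and the documents do not support them.

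- *That the missing baseline instrument proves follow-up use is meant.* It does not. Table 2 names no follow-up instrument for alternative treatments either, and the content of the baseline explanatory-model interview is not shown.
- *That use is a consequence of allocation.* The article does not say uptake differs by arm. Care managers monitor the treatment that the patient's own doctors recommended, which is not shown to be alternative treatment. T-CSCT patients also have access to consultation, and nothing bars them from psychotherapy. Dependence on arm is plausible, not stated.
- *That the simulated shifts forecast the bias.* Use rates and effects are assumed, and the planned random effects logistic models are not the linear ones used above.
- *That every outcome is touched.* No adjusted model is stated for patient or PCP satisfaction, and the stated power is reproduced by an unadjusted comparison of two proportions.

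The reply does not remove the point. The article does not leave the adjustment set open; it names this variable for all regressions. Its own account of the earlier trial, and the hope expressed in *PCP Involvement* of controlling for treatment outside the study, show that care received during the study is on the sponsor's mind. *PCP Involvement* describes a design measure, so it supports the follow-up reading without proving it.

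**Conclusion.** The point holds in conditional form. The plan puts use of alternative treatments into every regression without confining it to the time before randomisation. If use during follow-up is entered, and if it depends on allocation, the models stop estimating the intent-to-treat effect and the estimate can be biased upwards or downwards. A reader might infer that the treatment effect is biased as planned; the text does not go that far, because use before randomisation may have been meant.

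The documents do not determine the size. The illustrations show only that shifts of about 0.04 to 0.10 SD, or several percentage points of response, arise under unremarkable assumptions, and that a null effect need not stay null. Beside a planned difference of 30 points, some of these would matter. Two analysts could both follow the text as written, one using baseline use and one using follow-up use, and report different effects. That choice should be closed before anyone sees outcomes by arm.

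**What to change.** In the Analysis section, define the covariate as use of alternative treatments for depression recorded before randomisation, and say which treatments count; or drop it from the main models. Apply the same rule to the models for treatment initiation and trial completion.

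Report use of other treatments during follow-up by arm as a descriptive result. If an adjusted analysis on follow-up use is wanted, label it a sensitivity analysis and state that it does not estimate the intent-to-treat effect.

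The adherence rows of Table 1 should not stand in for this covariate. They belong to the care manager's schedule, the *Blind assessments* section reserves the blind raters' information for data analysis, the article does not say whether the screening column covers usual-care patients, and adherence is not the same variable.

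Cost: one sentence in the plan and at most one added baseline question. No extra visits, and no change to the 60 patients per arm.
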